## Abstract

**Background:**

Growing evidence suggests that mental health issues heavily impact Muslims, the largest, fastest growing minority religious group in the UK. High prevalence of anxiety and depression has been reported in young women aged 18 to 30 largely from Bangladeshi and Pakistani Muslim communities in Britain. Evidence suggests that incorporating religious and culturally adapted interventions may improve their effectiveness for Muslim populations, but their feasibility for young women in UK contexts is uncertain. This study aims to test whether a randomised controlled trial (RCT) of a faith-based intervention for young Muslim women living with depression is feasible.

**Methods:**

This study is a two-arm cluster randomised controlled feasibility trial with embedded process evaluation. Participants will be young Muslim women aged 18 to 24 years experiencing mild to moderate low mood or depression in Birmingham and London. The intervention will be delivered by trained therapists, supported by mental health support workers, once a week for 6 weeks. The two arms will be the IM-Adapted faith-based intervention and the standard NHS psychoeducation support group control with a proposed sample size of 30 per arm. Outcomes are referral, recruitment and retention rates, session attendance, adherence and acceptability of intervention, data collection, and adverse events, measured at baseline, 3 and 6 months.

**Discussion:**

The findings will provide early indication as to whether tailored mental health interventions may increase accessibility and effectiveness of support in underserved communities, addressing barriers linked to social and cultural factors. This will guide health services on the incorporation of cultural and religious adaptations in their programmes to better engage minority groups and improve mental health outcomes.

**Trial registration:**

ISRCTN, https://www.isrctn.com/ISRCTN17842222, registered 17th April 2024.

## Introduction

### Background and rationale

There is growing concern about the mental health and well-being of children and young people, with a striking sixfold increase in the prevalence of long-term mental health conditions in England from 1995 to 2014 in those aged under 24 [1]. Young people are particularly susceptible to the onset of mental illness, with over 50% of mental health problems emerging before the age of 14 and 75% before the age of 25 [2]. It is of concern that young women aged 16 to 24 have three times higher prevalence than men (26% vs 9%) with problems more common in young people from minority ethnic backgrounds [3, 4]. Females aged 24 years and under have seen the largest increase in suicide rates over the last three decades [5]. In England and Wales, rates amongst females aged 10 to 24 increased by 24% between 1992 and 2022, with a more substantial increase of around 41% over the last 20 years [5].

Growing evidence suggests that mental health issues can heavily impact Muslims; the largest, fastest growing minority religious group in the UK [6–9]. Particularly, high prevalence of anxiety and depression (over 35%) has been reported in young women aged 18 to 30 largely from Bangladeshi and Pakistani Muslim communities in Britain, who make up nearly two thirds of the British Muslim population. Around 45% of these women have reported struggling with mental health [10, 11]. Young Pakistani and Bangladeshi mothers have also reported high levels of depression (37%) during the pandemic [12]. While this evidence is diverse and contributes to a broader understanding of mental health challenges amongst Muslim women, it is predominantly observational. However, some studies adopt qualitative approaches, offering meaningful insights from lived experience, though they limit the ability to draw firm conclusions about underlying causes.

Muslim women are known to experience high levels of Islamophobia in European contexts [13] and perceived discrimination in young British Muslim students in the UK is associated with increasing anxiety and depression, with social stigma remaining strong [14, 15]. The higher prevalence rates are likely to reflect a complex interplay of factors such as social disadvantage, discrimination, and acculturative stress [16, 17].

It is concerning that Muslims are under-referred to therapy services for mental health problems and show poor recovery rates compared to the general population, resulting in inequalities in mental health care and sub-optimal treatment for mental health problems [18, 19]. Muslim women face various barriers when seeking help for mental health. Within the South Asian community, cultural discourses such as ‘sharam’ (shame) and ‘izzat’ (honour) have a significant role. These concepts and the negative discourse of mental health in these communities have the potential to deter young South Asian women from seeking help as they fear bringing dishonour and shame to their families and communities in situations where poor mental health is seen as ‘defect’ [20]. In addition, lack of awareness about mental health, services available and what the help actually involves, family responsibilities, stigma around mental health and fear of being negatively judged by the community are additional factors which make it difficult for Muslim women to access mental health services [21, 22].

There is an unmet need for intervention that is greatest in underserved and ethnic minority communities [7]. This can be explained, in part, due to lack of tailored support to meet the needs of diverse groups with evidence that standard Cognitive Behavioural Therapy (CBT) based interventions are not as effective in promoting mental health and wellbeing in ethnic minority communities [23]. The Covid-19 pandemic highlighted the impact of health inequalities with increased mortality in ethnic minority communities and the importance of tailored support that considers social, cultural, and religious attitudes, beliefs and norms [13, 24]. Tailored support provided at a local level, such as health champions, demonstrated increased reach and engagement with formal services during the pandemic [25]. Religiously and culturally tailored interventions that encourage young Muslims to understand and discuss mental health, and improve help-seeking behaviours, overall mental health, and well-being, need to be developed and tested.

Evidence suggests that incorporating religious and cultural adaptations in tailored interventions for Muslim populations may improve mental health and well-being through ‘positive religious coping’, drawing on internalised spiritual beliefs to promote a deeper acceptance (this is due to mental health stigma and guilt), hope and resilience [18, 26–28]. Mental health services using such interventions in clinical practice can show promise as engaging religious beliefs can have a positive impact on psychological distress [27, 28]. Positive engagement with Muslim identity can also counter discriminatory practices, particularly for women who are disproportionately subjected to Islamophobic abuse, stereotypes, and violence [10, 29, 30]. Women from these communities are also subject to a ‘Muslim penalty’ with respect to education outcomes, economic activity, and unemployment [10, 31] which can contribute to mental ill health. Religious identity is core for many Muslim people and needs to be considered for person-centred care in this group [10, 26, 32]. Although religious and cultural identities can be closely intertwined with cultural expressions often influenced by religious themes, they are distinct dimensions of identity [33–35]. Concerningly, mental health service providers often lack an adequate understanding of religious and cultural sensitivities and cultural competence, leading to inappropriate or ineffective interventions [36]. In addition, cultural concepts relating to the causes of mental illness and social stigma amongst British Muslims combine with service mistrust to adversely impact service use [22, 37].

Muslim-led organisations offer mental health interventions delivered by therapists and counsellors trained in Islamic Psychology [38]. These take a holistic approach to religion within Muslim communities, which mainstream mental health provisions lack [38]. It is suggested that a collaborative approach involving faith communities, charities, and mainstream mental health services working together to improve religious and cultural competency amongst mental health practitioners would allow for knowledge exchange and increase access for Muslim communities who are often referred to as ‘hard-to-reach’ [38–40]. The Perinatal Mental Health support for Muslim communities, a collaborative project between Cambridgeshire, Peterborough, and South Lincolnshire (CPSL) Mind and The Lantern Initiative, is a success example of how different organisations can work together to support the needs of underserved Muslim communities [41].

Our research similarly follows a collaborative approach, bringing together academics who have expertise in research amongst Muslim populations and faith-communities more generally, practitioners who deliver culturally adapted therapy, and experts-by-experience members. Collaborating with Inspirited Minds (IM), a Muslim-led mental health charity, to deliver this faith-based and culturally adapted therapy programme—IM-Adapted—will support our aim of establishing how to engage participation from within Muslim communities. Despite the growing evidence, impacts of mental health on Muslim communities and minority ethnic groups are underrepresented in research [42–44]. Some of the barriers to participating in research for minority groups include language, not knowing about research, stigma, trust, location, cultural awareness and competence, culturally matched researchers, and understanding the consent process [43, 45]. This feasibility study will be key for establishing whether our current strategies for recruitment and retention of participants have worked and whether strategies to optimise participation need to be adopted for a full randomised controlled trial (RCT) to take place.

Our research will address key public health challenges, including how best to engage with communities who do not access mental health services, delivering community/faith-based interventions in non-NHS settings to support young women, training practitioners in this novel approach, and using appropriate evaluation frameworks to capture process and outcomes [46, 47]. It will inform a pathway to testing the effectiveness and cost-effectiveness of the IM-Adapted intervention for young Muslim women, increasing representation of marginalised groups in research.

### Objectives

To establish the feasibility of conducting a full RCT of a faith-based culturally adapted intervention to promote and improve mental health and well-being of young Muslim women in community settings. It will determine whether it is possible to recruit and retain young Muslim women to the trial, develop and deliver the intervention as planned, evaluate the training and delivery of the intervention, explore the feasibility of collecting data, and will provide data to inform the design of the main trial.

### Trial design

A two-arm cluster randomised controlled feasibility trial delivered in groups in two locations (Birmingham and London). Clusters will each comprise 8–10 young Muslim women, with three groups at each site. This trial incorporates embedded mixed methods process evaluation.

## Methods: participants, interventions, and outcomes

### Study setting

The IM-Adapted feasibility trial will take place in Birmingham and London. The intervention will be delivered by trained mental health professionals, employed by the Inspirited Minds charity, in local mosques or community centres.

### Eligibility criteria

Individuals are eligible for inclusion if they are a Muslim woman aged 18 to 24 years, self-diagnosed or referred from another source with low mood or mild depression and scoring between 5 and 14 on the Patient Health Questionnaire 9 scale (PHQ-9) [48], who are willing to take part in the study, consent to participate, and are able to read and understand English.

Individuals will be excluded from the study if they do not meet the above eligibility criteria and are considered unsuitable based on the professional opinion of the IM’s mental health professionals eligibility screening and risk assessment (e.g. presenting significant risk) or their current treatment or co-morbid conditions present contraindications to engaging in the trial (e.g. severe chronic pain).

### Interventions

Participants will be randomised in groups of approximately 10, as soon as sufficient numbers have accrued at a site. Groups will be allocated to receive either the Inspirited Minds Adapted (IM-Adapted) programme (intervention arm) or the usual psychoeducation support group (control arm). The sessions will be run by a trained therapist supported by a mental health support worker (MHSW) and will be delivered once a week for 6 weeks, lasting approximately 90 min in a mosque or community centre.

#### Inspirited Minds adapted (IM-Adapted) intervention arm

For the purposes of this intervention, we define religion as “an organised system of beliefs, practices, and symbols designed to facilitate closeness to the sacred or transcendent (God, higher power, or ultimate truth/reality), and to foster an understanding of one’s relationship and responsibility to others in living together in a community” [49]. The IM-Adapted programme is a faith-based culturally adapted peer support group intervention aimed at promoting and improving mental health and well-being and tailored to the specific needs of Muslim communities. It was co-developed with Muslim service users and therapists. The IM-Adapted intervention (see Table 1 for key characteristics) is CBT-based and adapted with Islamic faith messages using cognitive and behavioural underpinnings including insights from GM’s (co-applicant) therapeutic approach with Muslim populations [18, 28] and CBT models used in cultural adaptations [50–52]. The intervention also uses a place-based community approach [53] by delivering in a mosque or community centre. It is delivered by Muslim women who are experienced practitioners and have previously been trained in the use of CBT by the NHS and co-facilitated with mental health support workers. Inspirited Minds staff delivering the IM-Adapted programme will receive additional training in the delivery of IM-Adapted via a training manual coupled with online workshop sessions.

**Table 1 Tab1:** Comparison of key characteristics of intervention and control arm group sessions

IM Adapted	Control group
Group run by Muslim women with standard NHS CBT training who have additionally received specialised training in the delivery of the IM-Adapted intervention	Group run by Psychological Wellbeing Practitioners who are Muslim women with standard NHS CBT training
Starting the treatment with the Dua (Islamic prayer)	Normal introductions to the session
CBT Components including the 5 areas model [56]	CBT components including the 5 areas model [56]
Supportive space to have open conversations, using questions around culture and religiosity to prompt discussion and hearing from others	Supportive space to have conversations without religious and cultural prompting
Islamic content and stories related to depression from the Quran and stories of the time of the prophet, having discussions around this	Not included
Homework setting	Homework setting
Journaling every week allowing time to reflect on cultural and religious learning from the sessions with prompted questions	Non-culturally or religiously informed journaling activity
Ending with cultural and religious reflections and key learning	Ending with general reflections and key learning
Ending with a Dua (Islamic prayer) for hope	Not included
Being provided with IM booklets around mental health, which is faith based	Booklet and content from the slides

The intervention recognises the broader cultural identities of young Muslim women and addresses issues of stigma, social structures, and religious explanations for depression. This involves creating positive messages from Islamic teachings that relate to positive religious coping, behavioural components linked to behaviour change theories, activity scheduling to address negative thoughts and improve mood and impact on behaviour, use of positive logs, journalling, goal setting, modelling positive behaviours, and the use of peer support to tackle loneliness and offer initial steps to improve low mood, address barriers, and improve access to support. This results in reduced stigma and allows individuals to feel more confident to seek support. It focuses on addressing negative beliefs and positive and negative coping through religious messages, thereby increasing positive beliefs about mental health [54, 55].

Themes addressed by IM-Adapted are the following:Culture and related issues including a lack of communication and understanding around mental health, a taboo subject, with guilt and beliefs of not being a good Muslim if you are struggling with your mental health.Capacity and coping strategies including limited adapted treatments to suit more Islamic ways of working and using faith as a way of coping and sometimes leading to use of recreational drugs to cope due to needing to mask symptoms.Cognition and beliefs, including rigid beliefs about mental health and assumptions that if people pray more, they will feel better.Isolation and stigma due to limited access to specialised treatments and not openly communicating with others and hence feeling like they are the only ones struggling with mental health.

#### Psychoeducation support group control arm

The comparison group is a low-intensity CBT psychoeducation group with no religious or cultural adaptation (see Table 1) delivered by qualified (Mental health professionals who have a core profession in psychology, for example, Psychological Wellbeing Practitioners, Counsellor, CBT Therapist) female Muslim mental health professionals from IM. As with the IM-Adapted intervention arm, control participants will receive six weekly sessions (90 min per session) in groups of approximately 10 women. The sessions will include components of CBT in a group format for low mood, including behavioural activation, activity scheduling, thought challenging, and understanding their pattern using a 5 areas diagram.

### Outcomes

The primary feasibility outcomes to determine progression to a future definitive trial are as follows:Number of participants referred, excluded, and recruited and reasons for not participatingRetention rates at follow-upParticipant engagement and adherence (sessions attended)Feasibility, acceptability, barriers and facilitators to interventions (process evaluation)Data quality and follow up completion rates, including health economic dataTraining and delivery model (adherence, engagement, confidence)Adverse event rateThe existence of early evidence that the intervention is not clearly inferior to usual careFeasibility of required sample size

We will measure a range of secondary outcomes with a view to making a decision about which to include in a future definitive trial. The secondary outcome measures (as potential primary outcomes for a definitive trial) are the following:

Distress, well-being, anxiety, overall health-related quality of life, loneliness, resource use and religious coping.

### Participant timeline

Table 2 shows the SPIRIT (Standard Protocol Items: Recommendations for Intervention Trials) [57] table detailing study processes.

**Table 2 Tab2:** SPIRIT (Standard Protocol Items: Recommendations for Intervention Trials)

	Study period						
	Screening	Randomisation	Post-randomisation				
Timepoint	Pre-T0	Pre-T0	T0	T0–T1	T1 + 6 weeks	T2 + 24 weeks	
**Enrolment:**							
Eligibility screen	X						
Referral to research team	X						
Informed consent	X						
Randomisation		X					
**Interventions:**				X			
**Assessments:**							
PHQ-9	X		X		X	X	
Demographics information	X						
GAD-7			X		X	X	
WEMWBS			X		X	X	
R-COPE			X		X	X	
EQ-5D-5L			X		X	X	
CSRI			X			X	
Measure of loneliness			X		X	X	
Adherence				X			
Focus groups							X
Adverse event monitoring				X	X	X	

*Note*: *T0* = baseline, *T1* = first follow-up, *T2* = second follow-up, *PHQ-9* = Patient Health Questionnaire, *GAD-7* = Generalized Anxiety Disorder, *WEMWBS* = The Warwick-Edinburgh Mental Wellbeing Scale, *R-COPE* = Brief Religious Coping Measure, *CSRI* = Client Service Receipt Inventory

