### Recruitment

Young women will be informed about the study through mosques and community groups supporting recruitment for the study and through IM’s usual referral processes, study website, and social media. Individuals will be directed to complete the online self-referral form held on the IM website.

Study staff at IM will review incoming referrals to their services, via their usual online form, to identify those who meet the initial eligibility criteria check (i.e. are the right age, gender and have reported low mood/depression scoring 5–14 on the PHQ-9). Those meeting the initial eligibility check will be contacted to introduce the study and set up a consultation via telephone or video call. This includes a standard risk assessment undertaken by IM staff to finalise eligibility for participation in the study.

Those who are ineligible based on risk or other eligibility criteria or do not wish to participate in the study will be offered the usual support provided by IM as appropriate. These individuals will be offered the option to give reasons for why they do not wish to participate in the study, but this question will be optional to avoid apparent coercion.

Those who meet all eligibility criteria for the study and would like to take part will be sent the link to the online (via REDCap) informed consent form.

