## Methods: assignment of interventions

### Allocation

Participants will be recruited and placed sequentially into a group at each site; once the group at the site has reached 10 participants, the group will be allocated. The allocated treatment for a group will be automatically generated via the study database. Stratification will be by study site (Birmingham or London) with a block size of 2. The groups will be allocated by a process embedded in the web-based data management system REDCap [61, 62] managed by the University of Hertfordshire Clinical Trials Support Network (UHCTSN) ensuring allocation concealment. When a group is randomised, an email will be sent to the principal investigator (PI) and the Trial Manager, who will communicate with the Therapist and MHSW to set up the appropriate group sessions.

Due to the nature of the intervention, allocation blinding is not possible. Where possible, both supporting staff will be blinded during data collection and statistical analyses will be blinded. 

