### Consent

Eligible young women will be asked to complete the online informed consent form. This form can be accessed by a link which will take them to the online form via the REDCap database held by the University of Hertfordshire. Participants will receive a copy of the signed informed consent form via email.

Consenting eligible women will then be recruited to the study and randomised either to the IM-Adapted intervention or the comparison group.

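### Table 2 schedules the baseline questionnaires after randomisation in an unblinded, self-report trial, so baseline answers and baseline non-response could reflect the allocated arm

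*Protocol article*

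**What the plan says.** The order of events is fixed in the Participant timeline section, Table 2. The Screening and Randomisation columns both carry the time label Pre-T0. T0 is the first column under the heading "Post-randomisation", and the table note reads "T0* = baseline, *T1* = first follow-up, *T2* = second follow-up". PHQ-9, GAD-7, WEMWBS, R-COPE, EQ-5D-5L, CSRI and the row "Measure of loneliness" are all marked at T0. Only PHQ-9 and "Demographics information" are also, or instead, marked at screening.

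Other sections bear on the order:

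- **Recruitment:** women pass the initial check if they are of the right age and gender and "have reported low mood/depression scoring 5–14 on the PHQ-9". This is the screening PHQ-9.
- **Consent:** "Consenting eligible women will then be recruited to the study and randomised". No baseline step is mentioned in between.
- **Allocation:** a group is allocated when it reaches 10 women. The principal investigator and Trial Manager are then emailed, and they arrange the sessions with the therapist and support worker. Completion of baseline is not a condition for allocation.
- **Allocation, on blinding:** "Due to the nature of the intervention, allocation blinding is not possible", followed by "Where possible, both supporting staff will be blinded during data collection and statistical analyses will be blinded".
- **Baseline and follow-up:** questionnaires are completed online on the women's own devices, with a telephone option. The section does not say whether baseline comes before or after allocation.

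**The concern.** A baseline measure is useful because it cannot have been influenced by the allocation. If it is taken afterwards, and the person answering may know her arm, that protection is lost. Here the arms differ in religious and cultural content, and one of the baseline scales is religious coping. A woman who knows she is in the faith-based group, or in the group without that content, might answer R-COPE or the well-being scale differently. She might also be more or less inclined to return the questionnaire.

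Blinding staff where possible, and blinding the analysis, does not help with this. The respondent is the participant, and no masking of participants is claimed.

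The trial is a feasibility study, but baseline data still matter in it. Completion of key measures is a traffic-light progression criterion, missing-data proportions are a stated result, and there is no imputation. The schedule tested here is also meant to inform the main trial.

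**Working it through.** The plan states no figure on this point, so the check is a reading of Table 2 by column, followed by a look at which results use T0.

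**Step 1. Table 2, column by column**

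| Column | Time label | Under the post-randomisation heading | Marked items |
|---|---|---|---|
| Screening | Pre-T0 | No | Eligibility, referral, consent, PHQ-9, demographics |
| Randomisation | Pre-T0 | No | Randomisation |
| Third | T0 | Yes, first column | All seven instruments |
| Fourth | T0–T1 | Yes | Intervention, adherence, adverse events |
| Fifth | T1 + 6 weeks | Yes | Six instruments (not CSRI), adverse events |
| Sixth | T2 + 24 weeks | Yes | All seven instruments, adverse events |

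The order is stated twice: by the spanning heading, and separately by the time label on the Randomisation column. A heading displaced when the PDF was read would not explain the second.

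**Step 2. Which instruments have a value from before randomisation**

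Seven are marked at T0. One of them, PHQ-9, is also marked at screening. That leaves 7 − 1 = 6 without one: GAD-7, WEMWBS, R-COPE, EQ-5D-5L, CSRI and loneliness. The screening PHQ-9 is limited to 5–14 by eligibility, but it does precede allocation.

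**Step 3. Does any text put baseline first?**

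No. Consent, Allocation, and Baseline and follow-up are all silent on it. The contrary order is stated only in Table 2.

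**Step 4. What a T0 shift would reach**

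Suppose knowledge of the arm moves the mean T0 score by d in one arm relative to the other.

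- Difference in follow-up means: contains no T0 term, so it is unaffected.
- Difference in change (follow-up minus T0): moves by −d. The Statistical methods section names no change-score or baseline-adjusted analysis. This therefore matters only if the progression item about not being significantly less effective than usual care is read from change.
- QALYs: the article estimates them from EQ-5D-5L at baseline, 6 and 24 weeks. Assume area under the curve by straight lines, with weeks counted from T0. The first segment is ½ × 6 × (u0 + u6) and the second is ½ × 18 × (u6 + u24). The weights are 3 weeks for u0, 3 + 9 = 12 for u6 and 9 for u24, total 24. Baseline carries 3/24 = 12.5% of the weight.
- Completion: five psychological measures are scheduled at T0, T1 and T2. If all three rounds count towards the completion criterion, T0 is one third of the scheduled forms. The Progression criteria section does not say which rounds count.

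The size of d cannot be derived from the document, and no value is assumed here.

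**The case against.** The strongest reply is that the link from schedule to bias is not documented. Bias requires that women know their arm when they answer T0, and nothing says when they are told. The allocation email goes to the principal investigator and Trial Manager, not to participants, and the statement that blinding is not possible says nothing about timing. This stands. A reader might infer that the baseline of all 60 women is already distorted, but the document supports only that they are exposed to the possibility.

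Second, the sentence in Consent is a condensed summary. It also leaves out the wait for a group to reach 10, so its silence on baseline proves little. This stands too. The case rests on Table 2, and the table could be mislabelled while the actual workflow is sound.

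Third, the analysis is descriptive, without hypothesis testing, and the study is not powered for efficacy. A reader might infer that the trial's arm comparisons are compromised. The document does not support that, because follow-up scores summarised by arm do not depend on T0 and no adjusted analysis is planned. Nor is PHQ-9 a good example of the harm, since it alone has a screening value.

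These replies limit the size of the problem. They do not remove it: the one place that fixes the order puts baseline after allocation, and no text corrects it.

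**Conclusion.** The point holds as a flaw in the stated schedule that should be fixed. Table 2 places T0 after randomisation, six of seven T0 instruments have no earlier value, and self-completion by unblinded participants leaves those data open to influence from the allocation. Whether any influence occurs is not known. It depends on when women learn their arm and on whether practice follows the table.

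The exposed results are:

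- baseline descriptives by arm;
- baseline completion and missingness;
- QALYs, through a baseline weight of 12.5% under the area-under-the-curve assumption;
- any reading of change from T0 in the effectiveness progression item;
- the schedule carried into the definitive trial, where a baseline-adjusted comparison would be far more likely.

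The feasibility aims as a whole are not undermined, and no efficacy conclusion in this trial rests on T0.

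**What to change.** Collect T0 after consent and before the group's allocation is generated or released, and show this order in Table 2, Consent and Allocation. One workable form:

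- When the tenth woman in a group consents, send the T0 links to all ten.
- Let REDCap release the allocation when all T0 forms are in, or when a short fixed window closes.
- Tell women their arm only after that.
- Flag any T0 form returned after release, so that it can be reported separately.

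If baseline already precedes allocation in practice, no change of workflow is needed. Correct the Table 2 labels and add a sentence saying when T0 is completed and when women are told their arm.

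The cost is a delay of a few days between a group filling and its allocation, plus a REDCap gate and a corrected table. No new measure or visit is required. The trial is recruiting, so the change protects only groups not yet allocated. For groups already allocated, the report should state whether T0 was completed before or after women knew their arm.
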